## Results

The clinical trial is ongoing. It was funded in December 2016, approved by institutional review board on April 25, 2017. Data collection started on September 19, 2017. As of May of 2020, enrollment has been completed (N=110 infants born moderately or late preterm). We aim to publish the results by mid-2021. The data sets from this study will be available by request from the corresponding author, once results have been published.

## Discussion

### Summary

This project is a logical continuation of the work in Bonifacino et al [38] and aims to contribute to the early detection of alarm signs in emotional development and early intervention to help infants born moderately or late preterm. Neonatologists have a central role to play in this regard, and based on the findings of both Bonifacino et al [38] and Facchini et al [40], we hypothesize that implementing interactive guidance intervention will reduce sustained social withdrawal in infants born moderately or late preterm compared to those who receive routine care. Also, we hypothesize that this interactive guidance intervention will be easily implemented and accepted by patients and their families.

This is the first randomized controlled trial that will be performed with infants born moderately or late preterm at follow-up pediatric checkups. The implementation of an interactive guidance intervention will allow Alarm Distress Baby Scale–trained professionals who use this interactive guidance intervention as a model to intervene for infants at risk.

### Study Limitations

One of the limitations of this study is the possibility that the parents of infants included in the intervention group will share information with parents of infants included in the control group. For this reason, twins are randomized together (both either in the control or in the intervention group). Additionally, all parents included in the study will be asked to refrain from sharing the written guides used in the study with others until the study is finished.

Another limitation is the pain protocol established at each institution. Clinica Alemana de Santiago has had a standardized pain protocol since 2012 that includes administering the Premature Infant Pain Profile every 3 hours while, in Hospital San Jose, the standardized pain protocol does not include the Premature Infant Pain Profile. Before the start of study recruitment, training was performed by nurses of Clinica Alemana de Santiago in order to teach the midwives in Hospital San Jose how to administer the Premature Infant Pain Profile. At Hospital San Jose, this is only done for the infants included in the study.

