### Protocol

For this study, in 2017, Bonifacino et al [38] conducted Alarm Distress Baby Scale training in Chile over 4 days which consisted of 30 hours and 12 training modules. The program featured 2 central theoretical modules which covered early interactions and emotional development, emotional deprivation and its consequences, social withdrawal behaviors as an early alarm sign, and the Alarm Distress Baby Scale fundamentals. Subsequently, 10 modules of video training were presented featuring material with infants between 2 and 24 months of age. These infants had attended medical checkups with Alarm Distress Baby Scale–trained and untrained pediatricians. Following the videos, there was an exam to certify the professionals in the use of the Alarm Distress Baby Scale. Fleiss kappa was used to determine if there was agreement between the 11 evaluators regarding diagnosis (normal behavior or sustained social withdrawal). There was a substantial agreement [44] between evaluators (κ=0.794, 95% CI 0.676-0.913; *P*˂.001). Individual kappa values for normal and sustained social withdrawal categories were κ=0.795 and κ=0.794, respectively.

One fundamental element of the training was that the professionals learned not only to detect the sustained social withdrawal behaviors (and to score these behaviors using the Alarm Distress Baby Scale), but also to meaningfully show the parents how—in terms of communication or contact—their infants seek interaction, with the objective of reducing sustained social withdrawal behaviors.

Participants of the study will be recruited during their admission to the neonatal intensive care units by members of the researcher team and enrolled and randomized by a study coordinator to either the intervention or the control group. The infant will be randomized in a 1:1 allocation using SPSS Statistics (version 25.0; IBM Corp), stratified by hospital center (Clinica Alemana de Santiago or Hospital San Jose) in blocks of four. Also, infants will be stratified into two groups, single or twin pregnancy, in order to isolate the intervention effect from that of other covariables (such as mother of twins learning). The Hospital San Jose sample will also be stratified into two groups, whether the infant is included or is not included in the Kangaroo Care program, since only Hospital San Jose currently offers this program that aims to promote mother infant bonding, and which could potentially act as a confounding variable.

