### Sample Size

We used the G*Power 3 software (Psychonomic Society Inc) to determine the minimum sample size required for obtaining a significant medium effect size (an effect size of 0.25), given α=.05 and a statistical power of 0.80 (β=.20), using the results presented in Bonifacino et al [37]. In Bonifacino et al’s study [37], the dependent variable was assessed in 4 different stages, with 3 of them involving the total sample. Also, between the second and third assessments, the control group received the intervention. Because of this, we considered the observed differences between the first and second assessments in order to compute our sample size (postintervention difference in prevalence of 57% for the control group and 13% for the intervention group). The resulting sample size estimate was 23 per group; however, in order to ensure a sufficient effect size and taking attrition into consideration, a sample size of 55 infants per group will be used.

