### Statistical Analysis

Two-tailed paired *t* tests will be used to compare covariates and dependent variables from the infant groups. A one-way analysis of covariance will be used to determine the effects of covariates (sociodemographic and neonatal intensive care unit hospitalization variables, postpartum depression, and posttraumatic stress) on the comparisons between groups (control and intervention) and between times (2, 6, and 12 months of corrected age medical checkups) regarding the dependent variable (sustained social withdrawal). Other statistical techniques such as matching, odds ratios, and logistic regression will also be used.

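### Twins are allocated as a pair, but the named analyses have no term for correlation within pairs, so standard errors for infant outcomes come out somewhat too small

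*Protocol article*

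**What the plan says.** - **Eligibility (Inclusion Criteria).** Infants from single and twin pregnancies may enter.
- **Allocation (Protocol subsection of Methods).** "The infant will be randomized in a 1:1 allocation using SPSS Statistics", in blocks of four, stratified by centre, by single or twin pregnancy and, at one hospital, by Kangaroo Care. The unit described is the infant.
- **Allocation of twins (Study Limitations).** To limit sharing of information between arms, "twins are randomized together (both either in the control or in the intervention group". For twins the unit is the pair.
- **Sample Size.** The estimate is made "given α=.05 and a statistical power of 0.80 (β=.20". It cites a "postintervention difference in prevalence of 57% for the control group and 13% for the intervention group" and reports: "The resulting sample size estimate was 23 per group". The target is then raised to 55 infants per group. Twins are not mentioned.
- **Statistical Analysis.** "Two-tailed paired *t* tests will be used to compare covariates and dependent variables from the infant groups". A one-way ANCOVA follows, with parental depression and posttraumatic stress among the covariates. Matching, odds ratios and logistic regression come last, in a list that is left open. No family or pair term appears.
- **Secondary Outcome Measures.** Parental depression and posttraumatic stress symptoms at 2, 6 and 12 months are also outcomes.

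**The concern.** Co-twins share parents, home, arm and whatever guidance the parents receive. The intervention works through the parents, so their withdrawal scores can be expected to correlate. The authors recognise the link, since they stratify on twin pregnancy (citing learning by mothers of twins) and keep pairs together. They deal with it in the allocation but not in the methods they name for the analysis.

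A two-sample t test, an ordinary ANCOVA and an ordinary logistic regression all treat each infant in an arm as an independent observation. When both members of a correlated pair are in the same arm, the variance of the difference between arms is understated. Confidence intervals are then too narrow and P values too small, including those for the primary outcome.

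Two features of the plan might seem to deal with this, but do not. Stratifying on twin pregnancy balances the number of twins between arms but does not model correlation within a pair. The words "Two-tailed paired" are not tied to twins in the text, and pairing co-twins who are in the same arm cannot give a comparison between arms.

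**Working it through.** **1. The plan's own figure.** Inputs from the Sample Size section: 57% versus 13%, α = 0.05, power 0.80; two-sided, as the Statistical Analysis section states for its t tests. The two-proportion formula gives 18 per group, or 22 with continuity correction. Fisher's exact test first passes 80% power at 22 per group (82.6%) and has 85.0% at 23. The stated 23 is thus reproduced to within one infant by a calculation that treats infants as independent. The section also quotes "a significant medium effect size (an effect size of 0.25" without naming the metric. A repeated-measures interaction with f = 0.25 gives exactly 46 in total (23 per group) with 2 measurements correlated at 0.3. No variant that was tried contains a clustering term.

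**2. Formulas.** Let t be the share of infants who are twins and ρ the within-pair correlation. With clusters of size 1 and 2 only:

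- design effect: DE = 1 + t × ρ
- naive SE ÷ true SE = 1/√DE
- actual two-sided type I error = 2 × [1 − Φ(1.96/√DE)]
- effective number per group = 55/DE

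**3. Inputs that the article does not give.** Neither t nor ρ is stated. Assumed: t = 10% to 50%; ρ = 0.3 to 0.7 for infant outcomes; ρ = 1 for a parent score entered once for each twin.

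**4. Results.**

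| t | ρ | DE | naive SE too small by | actual type I error | effective n of 55 | 23 × DE, rounded up |
|---|---|---|---|---|---|---|
| 10% | 0.3 | 1.03 | 1.5% | 5.4% | 53.4 | 24 |
| 30% | 0.5 | 1.15 | 6.7% | 6.8% | 47.8 | 27 |
| 50% | 0.7 | 1.35 | 14% | 9.2% | 40.7 | 32 |
| 10% | 1 | 1.10 | 5% | 6.2% | 50.0 | 26 |
| 30% | 1 | 1.30 | 12% | 8.6% | 42.3 | 30 |
| 50% | 1 | 1.50 | 18% | 11.0% | 36.7 | 35 |

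Worked example, third row: DE = 1 + 0.5 × 0.7 = 1.35; √1.35 = 1.162; 1.96/1.162 = 1.687; 2 × [1 − Φ(1.687)] = 0.092.

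**5. Check by simulation.** A two-sample t test with 55 per arm and 20,000 replicates gave a type I error of 6.7% at t = 30%, ρ = 0.5, and 8.1% at t = 30%, ρ = 1. At t of about 50% it gave 9.4% with ρ = 0.7 and 11.1% with ρ = 1. These agree well enough with the formula.

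**6. Sample size.** The inflated requirement is at most 35 per group, against 55 planned. At the smallest effective size (36.7 per group) power for 57% versus 13% is still about 98.8%.

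**The case against.** - **The list of methods is open, and a journal article condenses.** A cluster-robust error could be added to the logistic regression without changing its name, and an analysis plan that is not shown may do so. This stands as a limit on scope. A reader might infer that every analysis in the trial treats infants as independent; the article does not say that. It supports a claim about the methods it names, and a plain t test has no place for a family term.
- **The two statements on allocation need not conflict.** The limitations section can be read as clarifying a general rule. That is fair, and the rewording is minor. The unit is still misdescribed where randomisation is defined.
- **Parent questionnaires.** A reader might infer that parent outcomes are certainly worse affected. No section says that one parent's score is entered for each twin. Comparing these variables by infant group suggests it but does not establish it, and with one record per parent the duplication disappears. The ρ = 1 figures apply only to comparisons of duplicated parent scores between arms, not to the treatment effect on withdrawal when those scores serve as covariates.
- **Forces in the other direction.** Adjusting for covariates that twins share may lower the residual correlation. Unadjusted tests after stratified allocation tend to be conservative if the strata predict outcome. Both could offset part of the effect; neither can be quantified from the article.
- **Sample size.** A reader might infer that ignoring twins leaves the trial too small. On the plan's own assumptions it does not, as step 6 shows.

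**Conclusion.** The point holds for the analyses that the article names. Twins are eligible, co-twins share an arm, and the named methods carry no term for the pair. Standard errors for infant outcomes, including the primary one, are therefore too small if pairs were enrolled and their scores correlate positively.

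The size runs from negligible to moderate: design effect about 1.03 to 1.35 and type I error about 5.4% to 9.2%. Both ranges rest on an assumed 10% to 50% twins and an assumed ICC of 0.3 to 0.7. For parent depression and stress, a design effect of 1.1 to 1.5 and a type I error of about 6% to 11% apply only on the further assumption that one score is entered once per twin. The defect concerns the validity of intervals and P values, not the number recruited.

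**What to change.** 1. Reword the allocation text in the Protocol subsection: families are randomised, and twins share the allocation.
2. For infant outcomes, replace the plain t test, ANCOVA and logistic model with a model that clusters on family: a mixed model with a family random effect, or GEE or cluster-robust standard errors.
3. Analyse the parent questionnaires with one record per parent.
4. Report the number of twin pairs per arm, so that readers can judge the size of the effect.

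The article reports enrolment as complete, and none of this changes the design or the data collected. The cost is slightly wider intervals and the loss of the simple t tests as the between-arm analysis, so it is more than one added term in an existing model.

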### Ethical Considerations

The interactive guidance intervention does not involve any risk to the participating infants and parents. The neonatologists will follow routine medical care protocols at medical checkups and will only perform the interactive guidance intervention (verbally) if they detect sustained social withdrawal. Currently, the neonatologists on the investigation team are the only follow-up neonatologists trained in the Alarm Distress Baby Scale in Chile, so these infants will receive an evaluation and an intervention that is otherwise not currently available in either the public or in the private health system. Finally, if any infant scores 5 or higher on the Alarm Distress Baby Scale at the 12-month medical checkup (final assessment), they will be offered further assessment and intervention.
